### Study design

A mixed method study will be carried out, which will compare poorly controlled T2DM patients (poor glycaemic control was defined as an HbA1c value > 9% in the last test performed in the 12 months prior to study inclusion), treated with two different comprehensive approaches with a control group receiving only usual clinical care. The mixed methodology for the development of complex interventions composed of two phases: a first phase consisting of a qualitative study carried out through personal interviews with patients and professionals, and a second quantitative phase that will correspond to the execution of the clinical trial and in which the findings of the first phase will be applied.

We designed this study considering that the intervention group 2 will be the control group for Intervention group 1, where the specific monographic consultation is implemented. Group Intervention 1 includes the main intervention for which we will test the effectiveness to improve glycaemic control. In parallel to Intervention group 2, we decided to include an additional comparison group consisting of type 2 diabetic subjects attending primary care centres managed by our institution in our region, with subjects selected according to the same study criteria. To select this latter group, we describe the use of the Sistema d´Informació per al Desenvolupament de la investigació en Atenció Primària (SIDIAP) database, which contains anonymised electronic health records of patients attended at primary care centers of the same health care districts not participating in the study.

This study is non-randomized because it would be difficult give a different treatment to an individual in the same primary care center treated by the same professional without it affecting the outcome in the standard care arm of the study.

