### Characteristics of participants

The inclusion criteria include the following: T2DM of more than one year of disease duration, age between 30 and 80 years, HbA1c > 9% in the last test performed in the 12 months prior to study inclusion, with no change in antidiabetic treatment within the previous 3 months. The changes in the dose of a drug in the antidiabetic treatment will be not considered as exclusion criteria.

The exclusion criteria include the following: T2DM controlled by endocrinologist at the moment of inclusion, systemic glucocorticoid treatment (ATC code: H02AB) or orlistat treatment (ATC code: A08AB01) (chronic or during the two months prior to inclusion), estimated life expectancy < 2 years, active treatment for malignancy (other than basal cell cancer or squamous cell skin cancer), serious mental disorders (psychosis, bipolar affective disorder, severe depressive episode with psychotic symptoms), class III or IV (New York Heart Association functional classification) heart failure (ICD-10: I50), dementia, renal transplantation or current dialysis treatment, history of drug and/or alcohol abuse (ICD-10: F10-F14), pregnancy or lactation, treatment with immunosuppressive drugs, haemoglobinopathies (ICD-10: D58.2), or chronic anaemia, body mass index (BMI) > 45 kg/m^2^, or any conditions that the investigator considered could prevent the patient from completing the study.

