### Evaluation of the effectiveness in the three study groups

Data at baseline and at 12 months of the population of all three types of learning centres that meet the defined criteria for inclusion and exclusion will be compared. Criteria will be adequately defined using the ICD-10 codes, thoroughly specifying the temporary windows of the accepted values. Only the outcomes that include SIDIAP variables (as indicated in the Table 1) will be able to be evaluated; even those that are in the e-CRD will not be able to be assessed. This evaluation of effectiveness will be performed in two possible ways: i) following the patients who meet the inclusion criteria in 2015 until the end of the study in 2018 (cohort study), or ii) a cross-sectional study in 2015 and another in 2018.

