### Sample size calculation

The sample size was calculated using the GRANMO v.7.12 (IMIM, Barcelona) programme. Considering an alpha risk of 0.05 and a beta risk of less than 0.2 in a bilateral contrast, it was necessary to include 72 patients in each group (intervention and control) to detect a difference equal to or greater than 1% of HbA1c [5] between the two groups. A common standard deviation of 1.46 [6] and a loss rate to follow up of 20% were assumed.

Considering that each physician/nurse that makes up the Basic Care Unit will coordinate their diabetic patients, a correction may be made due to a possible contamination in the analysis between individuals by assigning each Primary Care Team to intervention or control groups and taking into account the design effect. According to a study performed by our research group [16], we estimated that each GP would have 15 potential candidate patients with HbA1c > 9%. Assuming that the intra-class correlation coefficient for Primary Care is 0.05 [29], resulting in a 1.7 design effect, the required sample size will be 42 * 1.7 = 72 individuals in each group.

Each control or intervention group consists of 3 basic health areas, one in each geographical area, each with a mean of 10 BCUs and 15 individuals per basic care unit. Thus, the sample finally calculated to obtain statistical significance was 72 subjects per centre, leading to a total of 648 study subjects.

First patient enrolled in the study INTEGRA on 09/12/2015.

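### Arm is fixed by centre and almost certainly known before patients are screened and consented, so IG-1 versus IG-2 is open to arm-dependent selection that the plan addresses only in part

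*Protocol article*

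**What the plan says.** All references are to the protocol article.

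- **Allocation.** Study design calls the study non-randomized. Sample size calculation deals with contamination by "assigning each Primary Care Team to intervention or control groups". Under Intervention group 1 and Intervention group 2, centre professionals receive the training, and only IG-1 centres run the monographic consultation.
- **Main contrast.** Study design states that "the intervention group 2 will be the control group for Intervention group 1", and names IG-1 as the intervention whose effectiveness is tested.
- **Entry of patients.** Participants must meet the criteria and sign consent (Phase 2, Participants). The last exclusion in Characteristics of participants is "any conditions that the investigator considered could prevent the patient from completing the study".
- **Numbers.** Sample size calculation describes three basic health areas per group, "each with a mean of 10 BCUs and 15 individuals per basic care unit", and concludes that "the sample finally calculated to obtain statistical significance was 72 subjects per centre".
- **Adjustment.** The Statistical analysis plan section compares baseline characteristics. If differences appear, it adjusts a linear regression for the variables identified, with a propensity score to be considered. A similar option exists for the outcome of HbA1c below 7%.
- **All-eligible evaluation.** Evaluation of the effectiveness in the three study groups says that "the population of all three types of learning centres that meet the defined criteria for inclusion and exclusion will be compared" at baseline and 12 months, using SIDIAP variables. It offers two designs: a cohort of patients meeting the criteria in 2015 and followed to 2018, or one cross-section in 2015 and another in 2018.

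**The concern.** Once a centre is assigned, every patient's arm follows from the centre. Staff in an IG-1 centre recruit to a new specialised consultation with visits at 0, 3, 6 and 12 months. Staff in an IG-2 centre recruit to the same package without the consultation and without the month 6 visit (Table 1 footnote). Who is approached, who accepts and who is judged able to complete can differ for that reason alone. The same exclusion wording need not select the same patients when the commitment differs.

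This is distinct from the volunteer difference against the SIDIAP controls. It acts between the two consenting arms, and randomizing the centres would not remove it. The Discussion concedes that volunteers tend to be more motivated, but treats this as common to all trials and answers it with large recruitment per centre. A larger sample does not shrink a difference between arms. Motivation and adherence are plausibly prognostic for HbA1c, so any such difference would be credited to, or taken from, the monographic consultation.

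**Working it through.** **1. The plan's own sample size.** Inputs from Sample size calculation: two-sided alpha 0.05, power 80%, difference 1 HbA1c point, SD 1.46, loss 20%, ICC 0.05, 15 patients per GP.

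- n per group = 2 × [1.46 × (1.96 + 0.842)]² / 1² = 33.46
- with loss: 33.46 / 0.8 = 41.8, so 42
- design effect: 1 + (15 − 1) × 0.05 = 1.7
- 42 × 1.7 = 71.4, so 72; 72 × 9 centres = 648

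The stated figures reproduce.

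**2. Room for selection.** 10 × 15 = 150 potential candidates per area and 72 / 150 = 48%. The 15 per GP are potential candidates with HbA1c above 9%, and the article does not say that they are net of the exclusions or of refusals. So 150 is an upper bound on the pool and 48% is a lower bound on the share of it that enters.

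**3. Possible size of bias (illustration).** Assumptions, none from the documents: one arm takes the upper share f of its pool on a trait correlated r with the 12-month HbA1c change; the other arm's entry is unrelated to that change; the SD of change is 1.46; no covariate adjustment is made. Then bias = r × i × 1.46, with i = φ(z)/f and z the cut-off that leaves share f above it.

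- f = 0.48: i = 0.398 / 0.48 = 0.83
- f = 0.72 (assuming that 100 of the 150 are eligible and willing): i = 0.337 / 0.72 = 0.47

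Standard error of IG-1 minus IG-2: effective n per arm = 216 × 0.8 / 1.7 = 101.6, and SE = 1.46 × √(2 / 101.6) = 0.205. With no true effect, the chance of p < 0.05 is Φ(bias/SE − 1.96) + Φ(−bias/SE − 1.96).

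| r | Bias, f = 0.48 | Chance of p < 0.05 | Bias, f = 0.72 | Chance of p < 0.05 |
|---|---|---|---|---|
| 0.1 | 0.12 | 9% | 0.07 | 6% |
| 0.2 | 0.24 | 22% | 0.14 | 10% |
| 0.3 | 0.36 | 43% | 0.21 | 17% |

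Selection in opposite directions in the two arms would double the bias. Equal selection in the same direction would cancel it.

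**4. What the plan sets against this.** The regression or propensity score depends on a baseline difference being observed and reaches only measured variables. In the all-eligible evaluation, a cohort defined in 2015 does not match recruitment, which ran from 9 December 2015 to 31 October 2017 (Control group). Two cross-sections do not follow the same patients. Neither option is linked to IG-1 versus IG-2.

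**The case against.** A reader might infer three stronger claims. The document supports none of them.

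- **That the plan does nothing about selection.** It provides for adjusted regression or a propensity score. Table 1 also shows the Patient Activation Measure, treatment satisfaction and quality of life at month 0 in both intervention arms. The Patient Activation Measure covers knowledge, skills, confidence and behaviours, so part of a motivation difference can be seen and adjusted for. What remains is that adjustment is conditional and that unrecorded motivation and investigator judgement escape it.
- **That eligible patients who did not enrol are never used.** The three-group evaluation can be read as comparing all eligible patients of the centres, and HbA1c is a SIDIAP variable. On that reading most of the remedy is already in view. What remains is that its design is undecided and it is not attached to the main contrast.
- **That half of the eligible patients are left out.** The 150 is not net of exclusions or refusals, and the Discussion expects low participation and wants as many candidates as possible. The true share may be well above 48%.

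It is also fair to say that one-arm truncation is an extreme model. Both arms share criteria and consent, and IG-2 differs only by the consultation, so selection may largely cancel. That staff know their arm is an inference, though a strong one, because they are trained for it. An invitation rule or screening log may be in the full protocol, so its absence from the article is not the point. Study design does give a reason for not allocating individuals within a centre, but that does not bear on selection after centres are assigned.

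**Conclusion.** The concern holds in limited form. Assignment by centre, consent afterwards and an open investigator judgement leave IG-1 versus IG-2 exposed to arm-dependent selection. The plan meets this with conditional adjustment for measured variables and an all-eligible evaluation that is not fixed.

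The documents do not show that bias occurred, in which direction, or how large it is. The range of 0.12 to 0.36 HbA1c points rests on the assumed r of 0.1 to 0.3, a 48% share, selection in one arm only, an SD of change of 1.46 and no adjustment. At a 72% share it is 0.07 to 0.21. Against a target of 1 point, such a bias would not create the whole planned effect, but under these assumptions it could noticeably raise the false-positive rate. This justifies an inexpensive strengthening of the analysis. It does not show that the main comparison is invalid.

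**What to change.** 1. **Evaluation of the effectiveness in the three study groups.** Commit to a sensitivity analysis comparing 12-month HbA1c between IG-1 and IG-2 centres in all registered patients who meet the coded criteria during each centre's recruitment period, enrolled or not. Fix it before outcomes are compared by arm. State that the estimate is diluted by the enrolled share: if only enrolled patients benefit, a 1-point effect at a 48% share appears as 0.48 × 1 = 0.48 points.
2. **Statistical analysis plan.** Make the IG-1 versus IG-2 adjustment unconditional, for baseline HbA1c, named prognostic covariates and the baseline Patient Activation Measure.
3. **Reporting.** Show baseline data for eligible and enrolled patients side by side, by arm.

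Weighting enrolled patients on recorded variables is not the main remedy, because it misses selection on unrecorded traits. Inviting patients in random order would come too late, since recruitment was to end on 31 October 2017.

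**Cost.** One further extraction from a database the study already uses, and one extra analysis. The all-eligible comparison needs each patient's centre but no marker of who enrolled, which helps because SIDIAP records are anonymised. The disadvantage is dilution. No added patients or visits are needed.

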**Methods:**

This is a two-phase mixed method study, whose aims are the development of complex interventions and the assessment of their effectiveness. The main study outcome is a change in glycated haemoglobin (HbA1c) levels.

The INTEGRA study is divided into two phases. Phase 1: A qualitative study with a phenomenological approach using semi-structured interviews with the objective of determining the factors related to the participants and health care professionals that influence the development and implementation of a specific intervention strategy aimed at patients with poor glycaemic control of T2DM in primary care. Phase 2: Exploratory intervention study to be conducted in Primary Health Care Centres in Catalonia (Spain), including 3 specific health care areas.

The intervention study has two arms: Intervention Group 1 and 2. Each intervention group will recruit 216 participants (the same as in the control group) between the ages of 30 and 80 years with deficient glycaemic control (HbA1c > 9%). The control group will be established based on a randomized selection from the large SIDIAP (Sistema d’Informació per al desenvolupament de la Investigació en Atenció Primària) database of patients with comparable socio-demographic and clinical characteristics from the three provinces.

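### The sample size of 72 per group uses a design effect for 15 patients per GP although whole care teams are assigned, and it becomes 72 per centre with no derivation and no power for the number planned

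*Protocol article*

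**What the plan says.** The inputs are all in the Sample size calculation section of the protocol article. The error rates are given as "Considering an alpha risk of 0.05 and a beta risk of less than 0.2 in a bilateral contrast", the target is "to detect a difference equal to or greater than 1% of HbA1c", and "A common standard deviation of 1.46 [6] and a loss rate to follow up of 20% were assumed". From these, "it was necessary to include 72 patients in each group (intervention and control"). The next paragraph expects 15 candidate patients per GP, takes an ICC of 0.05 for primary care, obtains a design effect of 1.7 and concludes that "the required sample size will be 42 * 1.7 = 72 individuals in each group". That paragraph also says that whole Primary Care Teams are assigned to the groups.

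The third paragraph gives each group three basic health areas, "each with a mean of 10 BCUs and 15 individuals per basic care unit", and ends: "the sample finally calculated to obtain statistical significance was 72 subjects per centre, leading to a total of 648 study subjects". The Methods part of the abstract agrees with this last figure: "Each intervention group will recruit 216 participants (the same as in the control group").

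The Study design section makes IG-2 the comparator for IG-1, the main intervention. It explains that care cannot differ between patients of the same professional in one centre. It draws the additional comparison group from SIDIAP records of centres in the same districts that do not take part.

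**The concern.** One calculation ends in two results that differ threefold: 72 per group, stated twice, and 72 per centre, which is 216 per group. The second is presented as following from the first, but nothing in between multiplies by three.

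The design effect is also set at a level where nothing is assigned. Treatment is assigned by care team or area, so patients are correlated within that unit and its size should enter the formula. A GP's list of 15 gives a much smaller inflation than an area of 72.

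The only power claim in the article therefore belongs to a number the trial does not use, at a level of clustering it does not have. A reader of a null IG-1 versus IG-2 result cannot tell what difference the trial was able to detect.

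**Working it through.** **Inputs** (all from Sample size calculation): two-sided alpha 0.05, power 80%, difference 1.0 point, SD 1.46, loss 20%, ICC 0.05, 15 patients per GP, three areas per group, 72 per centre.

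**1. The article's own figure.**
- n = 2 × (1.96 + 0.842)² × 1.46² / 1² = 33.5 per group.
- Loss: 33.46 / 0.8 = 41.8, so 42.
- Design effect: 1 + (15 − 1) × 0.05 = 1.70.
- 42 × 1.7 = 71.4, so 72.

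The 72 reproduces, but only with the design effect included. The first statement of 72, which lists only the error rates, difference, SD and loss, would give 42.

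**2. Design effect at the assigned unit.**
- 72 per area: 1 + 71 × 0.05 = 4.55, and 42 × 4.55 = 191 per group.
- On completers (72 × 0.8 = 57.6 per area): 1 + 56.6 × 0.05 = 3.83, and 33.46 × 3.83 / 0.8 = 160 per group.

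For areas of that size the need is therefore about 160 to 191 per group, above 72 and below the planned 216.

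**3. Power at 72 per group over three areas.** After loss there are 19.2 per area.
- Design effect 1 + 18.2 × 0.05 = 1.91.
- SE = 1.46 × √(2 × 1.91 / 57.6) = 0.376; noncentrality 1 / 0.376 = 2.66.
- Power: 76% by normal approximation, 60% by noncentral t on 6 df, 52% on 4 df.

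The 4 df are 2 × (3 − 1), for two groups of three areas. The 6 df are 3 × (3 − 1), pooling all three groups.

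**4. Power at 216 per group** (3 × 57.6 = 172.8 completers).
- Effective n = 172.8 / 3.83 = 45.1.
- SE = 1.46 × √(2 × 3.83 / 172.8) = 0.307; noncentrality 3.25.
- Power: 90% normal, 77% on 6 df, 69% on 4 df.
- Difference detectable with 80% power: 1.03 (6 df) or 1.16 (4 df).

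**5. Sensitivity to the centre-level ICC**, 216 per group after loss:

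| ICC | 4 df | 6 df | Normal |
|---|---|---|---|
| 0.01 | 96% | 99% | >99% |
| 0.02 | 90% | 95% | 99% |
| 0.03 | 82% | 89% | 97% |
| 0.05 | 69% | 77% | 90% |
| 0.08 | 54% | 62% | 77% |
| 0.10 | 47% | 54% | 69% |

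Power falls below 80% once the ICC exceeds about 0.033 (4 df) or 0.046 (6 df).

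**The case against.** The strongest reply is that the planned study is large enough by the method the authors used. Correcting the design effect gives at most 191 per group, the plan is 216, and normal-theory power is about 90%. The step to 72 per centre triples the sample and so raises power. This stands. A reader might infer that the two faults bring a stated 80% down to 69 to 77%, but the article does not support that. It states no power for 648, and the lower figures come from having only three centres per group, not from the design effect or the undocumented step.

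Those lower figures also need two assumptions. The first is that the ICC of 0.05 applies at centre level. The article calls it a primary care value and applies it to GPs; at a centre-level ICC of 0.02 the df-adjusted power is 90 to 95%. The second is a test on 4 or 6 df. The Statistical analysis plan section of the article describes t-tests, regression and a propensity score, and names no cluster-level analysis. Both assumptions have to be shown beside the figures.

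A reader might also see a contradiction between 10 units of 15 (150 per area) and 72 enrolled. There is none: the 15 are potential candidates, a pool from which 72 could be recruited.

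Finally, the article calls phase 2 exploratory, and a journal article condenses its protocol. That would excuse a missing detail. It does not excuse two incompatible results printed for one calculation, or a design effect for a unit that is not assigned.

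**Conclusion.** The point holds as a fault in the stated derivation. The design effect of 1.7 does not match the assigned unit, for which the same ICC gives 4.55 at 72 patients. The 72 per group misses beta below 0.2 at that unit after 20% loss by every method tried (76% normal, 52 to 60% on 4 to 6 df). The number actually planned, 216 per group, has no derivation and no stated power.

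It does not follow that the planned trial is underpowered. At 216 per group the answer runs from about 90% (normal approximation) to 69 to 77% (three centres per group allowed for) at a centre-level ICC of 0.05, and depends heavily on that ICC. The three-centre figures fit IG-1 versus IG-2 best. For the control group the number of centres is unclear: Sample size calculation gives it three basic health areas, whereas Study design and Control group describe records selected from non-participating centres across the three districts.

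**What to change.** In Sample size calculation:

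- Replace both statements of 72 in each group with 216 per group (72 per centre, three centres per group, 648 in total).
- Compute the design effect as 1 + (m − 1) × ICC with m the number of patients per assigned area, and say that the ICC of 0.05 is assumed to hold at that level.
- State the power for a 1-point difference after 20% loss as about 90% by normal approximation and about 69% (4 df) to 77% (6 df) when three centres per group are allowed for, with detectable differences of 1.16 and 1.03.
- Add the sensitivity to a centre-level ICC of 0.01 to 0.10, over which df-adjusted power falls from 96–99% to 47–54%.
- Reconcile the control group: three basic health areas, or records from non-participating centres across the districts. If the latter, give the number of centres and a separate power for comparisons with that group. This would not change IG-1 versus IG-2.

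The cost is a change of text with no added enrolment. The small downside is a less favourable stated power.
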